## Abstract

**Background:**

Cardiovascular disease (CVD) is a leading cause of morbidity and mortality in the Middle East and Africa (MEA), with a rising incidence particularly among women. Regional factors such as limited health care access, cultural barriers, and sex-specific risk factors exacerbate this burden. Despite this, women remain significantly underrepresented in cardiovascular research, and no large-scale, multicenter prospective trials have been conducted to provide national data. To address this gap, we established the Middle East African Registry Women Cardiovascular Disease (MEA-WCVD) to create a comprehensive database on the epidemiological profile and management of heart failure (HF), atrial fibrillation (AF), ischemic heart disease (IHD), and valvular heart disease (VHD) in women.

**Objective:**

The primary aim of this study is to compare the management of CVDs in women and men across MEA countries in accordance with current clinical practice guidelines. The study also seeks to identify gender-based disparities in health care insurance, income, and access to cardiovascular services.

**Methods:**

The MEA-WCVD is a prospective, multicenter, observational study enrolling consecutive patients aged ≥18 years with diagnosed HF, AF, IHD, or VHD across 25 tertiary care centers. Participants provide informed consent during a single visit, and trained investigators collect sociodemographic, clinical, and treatment data via electronic case report forms. The electronic case report form captures general characteristics (age, gender, and comorbidities) and diagnosis-specific details (imaging, guideline-based therapies, and complications). Data are stored in a centralized, contract research organization–managed database (Eshmoun-Clinical Research, Tunisia). An initial 75-day enrollment phase (May 2023-July 2023) is followed by a planned 1-year follow-up for outcome analysis. Data will be analyzed using SPSS (version 25) to compare gender disparities in management and outcomes using multivariable regression and survival analyses.

**Results:**

The MEA-WCVD study was funded in April 2023, and data collection began in May 2023. As of July 2023, a total of 15,366 participants have been enrolled across 25 centers. A 1-year follow-up is expected to be completed by July 2024. Data analysis is planned to commence in July 2024, with primary results anticipated for publication in March 2025. The study aims to establish the largest registry in the MEA region for HF, AF, IHD, and VHD, providing valuable insights into demographic trends, clinical management, and adherence to current guidelines.

**Conclusions:**

The MEA-WCVD registry will provide essential real-world data on the management and outcomes of the most prevalent CVDs (HF, AF, IHD, and VHD) in the MEA region. By directly comparing standard care management between men and women, this study will highlight gender disparities and inform future strategies for equitable cardiovascular care. The registry is expected to contribute to the largest contemporary cohort of patients with CVD in the region, advancing knowledge in cardiovascular epidemiology and clinical practice.

## Introduction

### Background

Numerous studies have uncovered substantial disparities in cardiovascular health between men and women, as well as among different subsets of women [1-3]. However, despite a growing global awareness, there remains a critical lack of region-specific data on the unique characteristics and management of cardiovascular diseases (CVDs) in women across the Middle East and Africa (MEA) region [4]. This research gap is particularly concerning as it contributes to the persistent underdiagnosis, undertreatment, and underresearch of common cardiovascular conditions such as ischemic heart disease (IHD), heart failure (HF), valvular heart disease (VHD), and atrial fibrillation (AF) in women.

Compounding this issue, several studies indicate that women with suspected heart disease are less likely than men to undergo recommended diagnostic testing and receive evidence-based treatments [3,5]. These disparities are further exacerbated by ongoing sex-based biases in clinical decision-making and the underrepresentation of women in cardiovascular research. While global research has increasingly acknowledged the influence of sex-specific pathophysiological, hormonal, and psychosocial factors in CVD, such insights are seldom translated into region-specific strategies, especially in low-resource settings.

In the MEA region, the challenges are magnified by limitations in health care infrastructure, sociocultural barriers, and insufficient awareness among both the public and health care professionals regarding the burden of CVD in women [1]. Moreover, existing prevention and treatment programs often fail to adequately address gender disparities, particularly in access to health care services, insurance coverage, and health education. These shortcomings are increasingly alarming given the demographic shift toward an aging population and the rising prevalence of cardiovascular risk factors in the region. This evolving epidemiologic landscape suggests a significant surge in CVD-related morbidity and mortality in the near future, with profound implications for public health systems.

In recent decades, Africa has seen a notable shift in the patterns of CVD, marked by a decline in rheumatic heart disease and a rising prevalence of noncommunicable conditions such as AF, HF, and IHD. While some national registries—such as those in Tunisia—have shed light on these trends [6,7], there remains a dearth of large-scale, gender-focused cardiovascular registries encompassing the broader MEA region. Notably, no comprehensive registry to date has centered on the cardiovascular health of women in this context, highlighting an urgent need for sex-disaggregated data to inform health policy and clinical practice.

### Research Gap

There is a lack of robust, sex-disaggregated, and region-specific data on the clinical presentation, management, and outcomes of CVDs in women within the MEA region. Existing studies and registries have largely overlooked gender-based analysis and fail to account for socioeconomic and structural determinants of health.

### Registry Objectives

The primary goal of the Middle East African Registry Women Cardiovascular Disease (MEA-WCVD) is to compare the diagnosis, treatment, and outcomes of major CVDs in women and men across participating MEA countries in alignment with current clinical practice guidelines.

The secondary objectives are to identify gender-based disparities in health care access, including differences in insurance coverage, income level, and health care use, as well as highlight any deviations from guideline-recommended care based on sex.

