### Clinical Assessment and Data Collection

During the office visit, the physician completes the electronic case report form (eCRF) of the registry after the patient’s approval according to the inclusion criteria.

To ensure the accuracy and completeness of the data, all centers involved in data collection adhere to standardized protocols for data entry, with regular training sessions provided to research personnel.

The eCRF is structured into 2 main sections. The first is a common data module that includes a comprehensive set of items pertaining to each patient’s sociodemographic profile and general clinical background. This encompasses variables such as age, sex, level of education, type of health insurance, socioeconomic status, degree of financial or physical dependence, and smoking status. Additionally, it records information on cardiovascular risk factors (eg, hypertension, diabetes, or dyslipidemia), past cerebro-cardiovascular events (such as stroke or myocardial infarction), coexisting pulmonary diseases, thyroid disorders (hypothyroidism or hyperthyroidism), and any history of cancer and related treatments. Key laboratory data such as creatinine and hemoglobin levels are also collected to assess renal function and anemia status, both of which are important prognostic factors in cardiovascular care.

The second part of the eCRF is diagnosis specific and tailored according to the patient’s primary inclusion diagnosis (HF, AF, IHD, or VHD). For each condition, this section captures detailed clinical information, including the etiology, findings from relevant imaging and laboratory tests, the use of guideline-directed medical therapy, occurrence of complications, and aspects related to medication adherence and reported side effects. This diagnosis-specific approach allows for a nuanced evaluation of each disease entity and facilitates meaningful comparisons between male and female patients across the MEA region.

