### Statistics

Data will be analyzed using SPSS (version 25; IBM Corp). To explore gender disparities in cardiovascular health outcomes and treatment effectiveness, data will be stratified by gender during analysis.

For the descriptive analyses, the Kolmogorov-Smirnov normality test will be performed for quantitative variables. Means and SDs will be used to describe quantitative variables when they are normally distributed. Otherwise, medians and IQRs will be used. Qualitative variables will be presented as numbers and proportions.

To compare frequencies based on gender, the Pearson chi-square test will be used when the application conditions are verified. Otherwise, the Fisher exact test will be used. To compare means based on gender, the Student 2-tailed *t* test for independent samples will be used when the 2 quantitative variables are normally distributed. If at least one variable is not normally distributed, the Mann-Whitney *U* test will be used. *P* values of less than .05 will be considered statistically significant.

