### Anticipated Findings

The primary analyses are expected to confirm disparities in cardiovascular care and outcomes between men and women, particularly in diagnostic approaches, therapeutic interventions, and access to care. For instance, we hypothesize that fewer women will undergo advanced imaging or invasive procedures or receive guideline-directed medical therapy compared to men. Furthermore, socioeconomic and health care access factors—such as insurance status and financial dependence—may further exacerbate these disparities in women. This comprehensive analysis will offer a deeper understanding of the structural and systemic barriers affecting cardiovascular care for women in the MEA region.

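### The guideline-care objective has no guideline-eligible denominator: the Statistics section gives only unadjusted comparisons by gender and does not carry through the regression announced in the abstract

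*Protocol article*

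**What the plan says.** - **Objectives.** Under Registry Objectives, the primary goal is given as: "compare the diagnosis, treatment, and outcomes of major CVDs in women and men across participating MEA countries in alignment with current clinical practice guidelines". A secondary objective is to "highlight any deviations from guideline-recommended care based on sex". The Hypothesis section likewise refers to appropriate and evidence-based care.
- **Analysis.** The Statistics section says that "data will be stratified by gender during analysis". For categorical variables it says: "To compare frequencies based on gender, the Pearson chi-square test will be used when the application conditions are verified", with Fisher's exact test as the fallback. Quantitative variables get a t test or a Mann-Whitney test. Significance is P<.05. Gender is the only stratifier; indication, eligibility and contraindication do not appear, and no regression model is mentioned.
- **Abstract.** Its Methods paragraph says the data will be analysed to "compare gender disparities in management and outcomes using multivariable regression and survival analyses". It names no covariates.
- **Expected result.** Anticipated Findings hypothesises that "fewer women will undergo advanced imaging or invasive procedures or receive guideline-directed medical therapy compared to men", without limiting this to patients with an indication.
- **Data.** Under Clinical Assessment and Data Collection, the diagnosis-specific part of the eCRF is described thus: "this section captures detailed clinical information, including the etiology, findings from relevant imaging and laboratory tests, the use of guideline-directed medical therapy". The common module adds creatinine and hemoglobin.

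**The concern.** A shortfall against a guideline is defined only for patients to whom its recommendation applies. The proportion treated among everyone with a diagnosis is a different quantity. It mixes patients with an indication, without one, and with a contraindication. Those shares may differ by sex, for example through type of heart failure, severity of a valve lesion, stroke risk or renal function.

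The objective needs a comparison conditioned on indication, and the tests set out in the Statistics section contain none. A team following that section literally could cross-tabulate treatment by gender within each diagnosis and report the result as a departure from guidelines. Part or all of the difference could then be case mix, or case mix could hide a real gap. The article intends its findings to inform policy, resource allocation and regional guidelines, so the distinction matters to its users.

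**Working it through.** The article gives no treatment rates, no eligibility shares and no split by sex or disease, so it has no figure of its own to reproduce. The calculation below shows the mechanism and its possible size. It does not estimate what this registry will find.

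**Inputs.** From the article: 15,366 enrolled, four diagnoses, P<.05. Assumed: equal allocation to diagnoses and sexes, 15,366 / 8 ≈ 1,921 per sex per diagnosis; a two-sided test; and all the rates below. Patients may have more than one diagnosis, so the equal split is a convenience.

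**Formula.** With s the share eligible, t the proportion treated if eligible and u the proportion treated if not eligible:

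- raw rate = s·t + (1 − s)·u
- if t and u are the same in both sexes, raw gap = (s_men − s_women)·(t − u)

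**Base illustration** (t = 0.80, u = 0.30 in both sexes):

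- Men, s = 0.60: 0.60 × 0.80 + 0.40 × 0.30 = 0.60
- Women, s = 0.50: 0.50 × 0.80 + 0.50 × 0.30 = 0.55
- Raw gap: 5 points. Gap among eligible patients: 0.
- SE = √[(0.60 × 0.40 + 0.55 × 0.45) / 1,921] = 0.0159; z = 0.05 / 0.0159 = 3.14; chance of P<.05 = Φ(3.14 − 1.96) ≈ 0.88.

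**Range.** Eligibility differences of 5 to 20 points give raw gaps of 2.5 to 10 points. The chance of significance is about 0.35 at 2.5 points and close to 1 at 10. With u = 0.50 the gaps are 1.5 to 6 points.

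**Second set of assumptions** (2,000 per sex, t = 0.80, men 60% eligible):

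| Women eligible | u | Raw rate, men vs women | Chance of P<.05 |
|---|---|---|---|
| 55% | 0 | 48% vs 44% | 72% |
| 55% | 0.20 | 56% vs 53% | 48% |
| 50% | 0 | 48% vs 40% | 99.9% |
| 50% | 0.20 | 56% vs 50% | 97% |
| 40% | 0 | 48% vs 32% | about 100% |
| 40% | 0.20 | 56% vs 44% | about 100% |

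A comparison restricted to eligible patients would reject about 5% of the time in every row.

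**Opposite direction.** Swap the base shares, so that 60% of women and 50% of men are eligible. Men's raw rate is 0.55. Women's raw rate is also 0.55 if 0.60·t + 0.40 × 0.30 = 0.55, that is t = 0.43 / 0.60 = 0.717. A true gap of 80.0 − 71.7 = 8.3 points among eligible patients would then show as no gap at all.

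**When there is no distortion.** From the gap formula, it vanishes if the share eligible is equal in both sexes or if t = u.

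**The case against.** The strongest reply is that the article nowhere makes all diagnosed patients the denominator. Chi-square or Fisher is also the natural test for treated versus untreated among eligible patients, and both the objective and the hypothesis can be read as already conditional on a recommendation. The abstract announces regression without restricting its covariates, so indication variables could enter it. Exact eligibility rules for each therapy usually sit in a full protocol or analysis plan, and neither is shown.

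Much of this stands. A reader might infer that the plan has chosen raw frequencies over eligible patients, and that women will therefore appear undertreated. The documents support neither step. The denominator is open, and the hypothesis quoted from Anticipated Findings is an illustrative sentence in the Discussion that fixes no analysis. The direction of any distortion depends on which sex is more often indicated, for which the article has no figure.

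The reply does not remove the point. The Statistics section does say how women and men will be compared: without adjustment, and by gender alone. That falls short of a guideline-concordance objective and of the abstract's own account of the analysis. Regression helps with this problem only if indication variables define the population or enter the model, and nothing says that they do. The point does not call for a list of therapy definitions; it calls for the guideline comparison to be conditioned on indication.

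**Conclusion.** The concern holds in a limited form. The comparison specified for a guideline-care objective is unadjusted and not conditioned on indication, and the Statistics section and the abstract disagree on whether regression is used. Taken literally, the text leaves the sex comparison open to differences in indication, in either direction.

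The 5-point base gap, like every rate and probability above, rests on assumed eligibility shares, treatment rates and an even split. These figures show that modest case-mix differences can matter at this registry's size, and nothing about its actual data. It would go too far to say that the plan is bound to manufacture a finding of undertreatment. The amendment is worth making before the analysis is run.

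**What to change.** Amend the Statistics section for the guideline-care objective:

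1. For each disease, make the main comparison the proportion treated among patients with the guideline indication, derived as far as possible from the etiology, imaging, laboratory and clinical fields in the eCRF. Exclude contraindications only where they are recorded; the article lists creatinine and side effects but no dedicated contraindication field.
2. Report the adjusted women-versus-men difference with a 95% CI from the regression named in the abstract, so that the two sections agree.
3. Show by sex the share eligible and the share whose eligibility cannot be determined.
4. Keep the raw chi-square or Fisher comparisons as descriptive.

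The article describes most of the needed fields as already collected, so the work is wording and derivation of eligibility flags. The price is precision and some unclassifiable patients. Under the base assumptions, about 1,153 men (0.60 × 1,921) and 960 women (0.50 × 1,921) remain. With 80% treated in each sex, the unadjusted 95% half-width is 1.96 × √(0.16/1,153 + 0.16/960) ≈ 3.4 points, against 1.96 × 0.0159 ≈ 3.1 points for the raw comparison.

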### Hypothesis

We hypothesize that women in the MEA region with CVDs are less likely than men to receive appropriate diagnostic evaluation and evidence-based treatment, resulting in suboptimal clinical outcomes. Furthermore, we expect that socioeconomic factors such as limited health care coverage and reduced access to specialized services disproportionately affect women’s cardiovascular care.

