### Inclusion and Exclusion Criteria

Patients (men and women) are officially enrolled in the MEA-WCVD study only if they are aged >18 years and have at least 1 of the following 4 diagnoses: HF, AF, IHD, or VHD.

Individuals are excluded if they present with CVDs other than the 4 target conditions. Additionally, patients who are unable to provide informed consent—due to cognitive impairment, communication barriers, or other medical or legal reasons—or those who explicitly refuse to participate in the study are also excluded.

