### Ethical Considerations

This study is conducted in compliance with the principles outlined in the Declaration of Helsinki. The MEA-WCVD (ClinicalTrials.gov ID: NCT05869214) received ethics approval from the South Tunisian Persons’ Protection Committee (0496/2023). The protocol was reviewed and approved as a multicenter study involving both hospital-based and private practice cardiology consultations.

All eligible participants are enrolled only after providing written informed consent during a single outpatient cardiology visit. Investigators ensure that participants fully understand the objectives of the registry, the voluntary nature of their participation, and their right to withdraw at any time without any impact on their medical care.

Data collected via the eCRF include anonymized and pseudonymized identifiers. No identifiable personal data (eg, names, addresses, or national IDs) are stored in the analysis database. All data are securely transferred and stored in a centralized, certified, and encrypted database managed by the contract research organization (Eshmoun, Tunisia).

No financial or material compensation is provided to participants. Participation in the study is voluntary, and no incentives or reimbursements are offered to avoid coercion or bias.

No identifiable photographs, images, or multimedia files of participants are included in this manuscript.

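### Enrolment is conditional on a diagnosis and a cardiology visit, so the registry cannot estimate sex differences in being diagnosed or in reaching cardiology, and its access and diagnosis aims should be limited accordingly

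*Protocol article*

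**What the plan says.** **Aims.** The abstract's Objective is to "identify gender-based disparities in health care insurance, income, and access to cardiovascular services". Registry Objectives makes the sex comparison of diagnosis, treatment and outcomes the primary goal. It makes health care access secondary, and lists insurance, income and use of care as components of access. The Hypothesis section expects women to be "less likely than men to receive appropriate diagnostic evaluation and evidence-based treatment" and adds that "limited health care coverage and reduced access to specialized services disproportionately affect women". Anticipated Findings expects the primary analyses to confirm disparities, access to care among them, and to throw light on structural barriers.

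**Entry.** Under Inclusion and Exclusion Criteria, patients must "have at least 1 of the following 4 diagnoses: HF, AF, IHD, or VHD". The abstract's Methods describes patients "with diagnosed HF, AF, IHD, or VHD across 25 tertiary care centers". Study Design names hospital and private cardiologists as recruiters. Ethical Considerations says that participants are "enrolled only after providing written informed consent during a single outpatient cardiology visit". Those unable to consent, "due to cognitive impairment, communication barriers, or other medical or legal reasons", are left out.

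**Data.** Clinical Assessment and Data Collection records imaging and laboratory findings, guideline therapy and complications for each diagnosis, and also insurance, socioeconomic status and dependence.

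**Limitations.** Strengths and Limitations mentions selection bias in general terms, with no mechanism or direction and no link to diagnosis or access.

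**The concern.** Some of the stated aims concern steps that every participant has already completed. A woman who was never diagnosed, never referred or never reached a cardiologist cannot be enrolled, and no group of suspected, undiagnosed or non-attending patients is described for comparison. Follow-up does not help, because it starts from the same enrolled patients.

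The stake is interpretation. The Dissemination Plan intends to share findings with health authorities, medical societies and advocacy groups. A small or null sex difference among attenders could be taken as reassurance about access or diagnosis, when the women with the worst access had no route into the data. The article's present wording does not guard against that.

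**Working it through.** The article gives no figure to reproduce here. Its target of 2000 women in Tunisia comes with no rates or power statement, and the point does not depend on it.

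**Step 1: what eligibility fixes.** Let D be holding at least one target diagnosis, C be having reached a cardiologist, and E be enrolled. The entry rules make E imply both D and C. So P(D | E) = P(C | E) = 1 in women and 1 in men, and each sex difference is 1 − 1 = 0 whatever the population difference and whatever the sample size. This follows from the entry rules and is not a detail that an analysis plan could supply.

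**Step 2: what still varies.** Imaging, procedures, therapy, insurance, socioeconomic status and dependence differ between attenders and can be compared by sex. To show that such contrasts are informative, take 2000 women (the target), an assumed 2000 men, assumed rates of 60% and 65%, and two-sided alpha of 0.05 (the Statistics section uses .05):

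- SE = √(0.60 × 0.40/2000 + 0.65 × 0.35/2000) = √(0.00012 + 0.00011375) = 0.0153
- 0.05/0.0153 ≈ 3.27, and 3.27 − 1.96 = 1.31, so power is about 90%

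**Step 3: how conditioning on enrolment may distort these contrasts.** Let p be the true proportion appropriately evaluated, a the probability of being diagnosed and seen in cardiology if evaluated, and b the same probability if not. By Bayes' rule:

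P(evaluated | enrolled) = p·a / (p·a + (1 − p)·b)

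All inputs are assumptions: p = 0.60 in women and 0.75 in men (true gap 15 points), a = 0.90, and b varied but equal in both sexes.

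| b | Women, enrolled | Men, enrolled | Observed gap (points) |
|---|---|---|---|
| 0.90 | 60.0% | 75.0% | 15.0 |
| 0.60 | 0.54/0.78 = 69.2% | 0.675/0.825 = 81.8% | 12.6 |
| 0.30 | 0.54/0.66 = 81.8% | 0.675/0.75 = 90.0% | 8.2 |
| 0.10 | 0.54/0.58 = 93.1% | 0.675/0.70 = 96.4% | 3.3 |
| 0 | 100% | 100% | 0 |

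The gap shrinks as entry depends more on having been evaluated, and vanishes only at the extreme.

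**Step 4: is the direction certain?** Let b differ by sex, using values already in the table.

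- Women 0.30, men 0.90: 81.8% vs 75.0%, so the gap reverses to −6.8 points.
- Women 0.90, men 0.30: 60.0% vs 90.0%, so the gap widens to 30.0 points.

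The first pattern fits the article's own premise that poorly served women are the harder to reach, so attenuation is the likelier direction. The second shows that it is not guaranteed.

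**The case against.** A reader might infer that the registry cannot test its hypothesis at all. The documents do not support that. The hypothesis concerns women who have cardiovascular disease. Anticipated Findings illustrates it with lower use of advanced imaging, invasive procedures and guideline therapy, and the case report form collects condition-specific imaging and treatment data. Evidence-based treatment is plainly testable among diagnosed patients. This part of the objection stands, and the point is limited accordingly.

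Nor has everyone enrolled obtained all the access in question. Registry Objectives includes insurance, income and use of care under access. These vary among attenders, and one cardiology visit is not access to imaging or procedures. This also stands. What remains out of reach is first diagnosis and arrival in cardiology, which the abstract's broader wording and the hypothesis on specialised services do not set apart.

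A reader might also try to size the effect by assuming that 50% of diseased women and 70% of men reach cardiology, and that 80% of each are then treated. That gives 0.50 × 0.80 = 40% against 0.70 × 0.80 = 56%, a 16-point population gap, beside 80% against 80% in the registry. But the zero registry gap is an input there, not a result, and patients who never reach cardiology are assumed untreated. It should not be used as an estimate.

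Three further points limit the claim. Underdiagnosis appears only in the background and the article draws no conclusion on it, so there is none to withdraw. No screening log is described, so a table of exclusions by sex cannot be presumed available. Finally, conditioning on diagnosis is normal for a disease registry and is openly stated, and selection bias is acknowledged. That is fair, but a general acknowledgement does not tell the reader which of the stated aims it affects.

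**Conclusion.** The point holds in a limited form. Sex differences in being diagnosed at all and in reaching cardiology care are not estimable, because both are fixed at 100% in each sex by the entry rules. This rests on the article's text alone and needs no assumed rate.

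Sex differences in work-up, procedures, therapy, insurance and socioeconomic status are estimable, but only for diagnosed patients already in outpatient cardiology care. As statements about all women and men with these diseases they may be distorted. Attenuation is probable if poorly evaluated women are the likeliest to be missing, but it is not certain. The size is unknown: the reduction from 15 points to between 12.6 and 3.3, and the reversal and widening, illustrate assumed rates and are not estimates for this registry.

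**What to change.** Enrolment closed in July 2023, so the change is to wording:

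- In the abstract's Objective, Registry Objectives, Hypothesis and Anticipated Findings, restrict the diagnosis and access statements to diagnosed patients already in outpatient cardiology care.
- Present insurance, income and dependence by sex as characteristics of attenders, not as estimates of access to cardiology.
- In Strengths and Limitations, replace the general mention of selection bias with three statements: enrolment is conditional on diagnosis and cardiology attendance; the likely, though not certain, direction is attenuation; and a small or null sex difference is not evidence of equal access or equal diagnosis.

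No new data or analyses are needed. The cost is a narrower claim.
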